## Abstract

**Background:**

Cigarette smoking is a leading cause of morbidity and mortality. For adults who smoke cigarettes and cannot or will not quit smoking, smoke-free products, such as nicotine pouches, have been recognized as a potential alternative to smoking combusted cigarettes to reduce harm due to cigarette smoking. The role of flavors in these smoke-free products in tobacco harm reduction has not been fully understood.

**Objective:**

This study evaluates the effect of flavors in *on!* nicotine pouch products (research products) in the reduction of cigarette smoking among adults who smoke cigarettes in their natural environment.

**Methods:**

This study uses a sequential, multiple assignment, randomized trial design. Approximately 400 eligible adults who smoke cigarettes will be enrolled and randomized to have access to either the Original (unflavored) *on!* nicotine pouch product only or a complete flavor profile (ie, Berry, Cinnamon, Citrus, Coffee, Mint, Original, and Wintergreen) of *on!* nicotine pouch products. After 3 weeks, participants in the Original-only arm will be randomized again, with half remaining in the Original-only arm and half having access to the complete flavor profile for another 3 weeks. Primary outcomes are expired-air carbon monoxide (CO) levels. Secondary outcomes are self-reported cigarette consumption and CO-verified cigarette abstinence.

**Results:**

Recruitment and data collection started in September 2023 and is projected to last until March 2025. We anticipate completing the data analysis in 2025. As of May 2024, we have enrolled 314 participants.

**Conclusions:**

This study will provide empirical evidence about the effect that flavor availability in smoke-free products may have in reducing cigarette smoking.

**Trial Registration:**

ClinicalTrials.gov NCT06072547; https://clinicaltrials.gov/study/NCT06072547

**International Registered Report Identifier (IRRID):**

DERR1-10.2196/56565

## Introduction

Smoking tobacco cigarettes is the leading cause of preventable morbidity and mortality in the United States, with approximately half a million attributable deaths each year [1,2]. The vast majority of smoking-related diseases are caused by inhaling harmful and potentially harmful constituents (HPHCs) present in tobacco smoke as a result of combustion [3,4]. While not entirely risk free, nicotine is not directly responsible for most of the harm caused by smoke exposure from combusted tobacco products [5]. The US Food and Drug Administration (FDA) and public health experts acknowledge that nicotine and tobacco products exist along a continuum of risk, ranging from combusted products posing the highest risk and noncombusted products at the lower end [5-8]. Complete tobacco cessation is the best option for reducing smoking-related morbidity and mortality for the 28.3 million adults who smoke cigarettes in the United States [9]. Nonetheless, tobacco cessation is often a protracted process that can span over multiple years for many adults who smoke cigarettes [10]. For adults who smoke cigarettes who cannot or are unwilling to stop smoking cigarettes, switching completely or replacing most of their combusted cigarettes with smoke-free nicotine products may be a viable harm-reduction option [11].

Oral tobacco-derived nicotine products are a relatively new category among the growing field of smoke-free nicotine products. Within this growing category are nicotine pouches (NPs), which contain pharmaceutical-grade nicotine derived from tobacco (but are tobacco-leaf free) along with flavors and other food-grade ingredients [12]. These products are commercially available in the United States in a wide variety of flavors (eg, mint, fruit, tobacco, coffee, and unflavored), with nicotine levels typically ranging 1.5-8.0 mg (with some brands offering levels up to 50 mg) [12-14]. NPs typically contain significantly lower levels of HPHCs than cigarette smoke [15,16], and switching from combusted cigarettes to these products has been shown to significantly reduce HPHC exposure to the user [17], positioning these products to serve as a potential reduced-harm option for adults who smoke cigarettes. Among the few studies assessing the longitudinal use of NPs among adults who smoke cigarettes, initial evidence suggests that adults who smoke cigarettes may switch to these smoke-free products or use them to help reduce cigarette consumption.

To date, we are aware of only 2 published studies of switching behavior or smoking reduction over time among adults who smoke cigarettes provided with NPs [13,18]. Campbell et al [18] provided participants with free choice among NPs in 2 flavors—mint or citrus—in a single nicotine level (4 mg) to use ad libitum for 6 weeks. At the end of the study, the majority of participants (79/97, 82%) reduced cigarette consumption, with 16% (15/97) reducing by ≥50% and 3.1% (3/97) self-reporting stopping smoking. No switching behavior outcomes were reported. This pilot study was intended to refine procedures and was not adequately powered to detect significant effects of using the research product on smoking reduction outcomes. Becker et al [13] examined longitudinal ad libitum use of NPs over 6 weeks among adults who smoke cigarettes (n=399). When provided with NPs in 7 flavors (ie, cinnamon, citrus, coffee, berry, mint, original, and Wintergreen) and 5 nicotine levels (ie, 1.5, 3, 3.5, 4, and 8 mg), 27% of adults who smoke cigarettes completely switched from cigarettes to NPs. Additionally, 39% reduced cigarette consumption by ≥50%, and 24% reduced their consumption by up to 49%. Interestingly, Becker et al [13] reported a positive association between the number of flavors used and the magnitude of cigarette reduction. Overall, these studies provide strong initial evidence that, in the context of free product provision, adults who smoke cigarettes are willing to switch to NPs, and those who do not completely switch can have meaningful reductions in their cigarette consumption when using NPs. Although they provided some initial insights about the potential role of flavors, the observational nature of these studies (eg, uncontrolled, no comparator groups, and no randomization) preclude the inference of causal relationships between NP use (regardless of flavor) and cigarette reduction.

The examination of available NP sales data shows that flavored varieties (eg, mint and fruit) consistently outsell nonflavored or “Original” varieties [19]. However, these data do not provide information on consumers’ concomitant use of other tobacco products (ie, switching or cigarette reduction). We designed this protocol to fill the knowledge gap and provide important information on the role of NP flavors on switching behavior and cigarette reduction among adults who smoke cigarettes (ClinicalTrials.gov NCT06072547). Specifically, this study uses a sequential, multiple assignment, randomized trial (SMART) design [20,21] to assess the effect of the availability of flavored (vs unflavored) *on!* brand NPs—holding nicotine level constant at 4 mg per pouch—on the smoking behavior of adults who smoke cigarettes over 6 weeks. Our purpose in this paper is to describe the protocol for a SMART study involving sequential randomization of adults who smoke cigarettes to provide evidence from an experimental study to advance the understanding of the role of NP flavors in smoking reduction. Our study objectives are to assess the following:

The overall effect of the availability of a complete flavor profile of the research products on smoking reduction among adults who smoke cigarettes.The effect of the availability of the complete flavor profile of the research products on smoking reduction maintenance among participants who reduce their cigarette consumption ≥50% at week 3 (ie, responders).The effect of the availability of the complete flavor profile of the research products on the smoking reduction at week 6 among participants who did not reduce their cigarette consumption ≥50% at week 3 (ie, nonresponders).The effect of early versus delayed availability of complete flavor profile of the research products on smoking reduction.

We hypothesize that access to a complete profile of flavored NP products will result in greater reduction, including greater persistence of reduction, in exposure to a smoking-related toxicant (ie, carbon monoxide [CO]) and cigarette consumption. With objectives 1-3, we intend to assess the hypothesis from 3 different angles (ie, overall effect, maintenance of reduction among responders, and additional reduction among nonresponders). With objective 4, we seek to explore the potential effect of a delayed access to flavored products, which may have regulatory implications for the speed of decision-making on flavored products. We consider objective 4 to be exploratory because it is difficult to simulate such a scenario in a trial context with limited follow-up time.

## Methods

### Study Design

#### Overview

This study will use an open-label randomized controlled trial design to evaluate the impact of availability of flavored versus nonflavored (ie, Original) *on!* 4-mg NP products on cigarette smoking among adults who smoke cigarettes. This study involves a remote screening visit, a baseline assessment period (3-7 days), 6 weeks of at-home product use, and a 6-month posttrial follow-up survey. Figure 1 provides a depiction of the study design (baseline assessment prior to week 1 and 6-month follow-up are not shown).

**Figure 1 figure1:**
[figure not shown]
Depiction of study design. Responders are participants who have a ≥50% reduction in cigarette consumption at week 3 (relative to baseline assessment); nonresponders are participants who have a <50% reduction in cigarette consumption at week 3 (relative to baseline assessment). R: random assignment.

#### Randomization

Approximately 400 participants will be recruited over an approximately 7-month period. After confirming eligibility and obtaining informed consent, participants will be randomized into 3 groups varying only by the availability of research product flavors. Group I (n=150) will have access to the complete flavor profile of the research products (ie, Berry, Citrus, Cinnamon, Wintergreen, Mint, Coffee, and Original). Group IIa (n=125) will have access to only the Original variety for the entire 6-week trial period. Group IIb (n=125) will have access to only the Original variety for the first 3-week period and will be provided access to the complete flavor profile for the second 3-week period. We chose to randomize participants to these 3 groups at study onset rather than have sequential randomizations (ie, first randomize to the full flavor profile or Original-only arm, then rerandomize those in the Original-only arm to either the full flavor profile or remain with the Original-only arm) to simplify the logistics of randomization.

#### Baseline Assessment

After randomization and prior to week 1, participants will be asked to track their daily cigarette consumption via a web-based daily diary and provide ≥2 biometrically verified expired-air CO readings via Bluetooth-enabled remote CO monitor (iCOquit Smokerlyzer, Bedfont Scientific) over a period of 3-7 days. These initial data will serve as baseline cigarette consumption and CO for subsequent comparisons.

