At the baseline telehealth session, participants will be further assessed for eligibility with additional inclusion or exclusion criteria, including a biometrically verified expired-air CO reading. If eligible, they will be randomized to Group I or Group IIa/IIb. During the 3- to 7-day baseline assessment period, participants will provide CO readings every other day and record their cigarette consumption in web-based daily diary survey. Upon the completion of the baseline assessment period, participants will begin week 1 when they receive the research product to use in their natural environment, following group configurations shown in Figure 1. During weeks 1-6, participants will respond to daily diary surveys to report their use of the research product (by flavor, if applicable), cigarette consumption, and use of other tobacco products. They will request and receive research products weekly. They will also be alerted to provide pseudorandom biometrically verified CO readings once every 3 days. At the end of week 3, female participants of childbearing potential will be asked to provide urine pregnancy test results; those with positive results (ie, pregnant) will be discontinued from the study and referred to their primary care provider. Six months after the study ends, participants will be recontacted to complete a follow-up survey with questions related to tobacco-use behaviors (including cigarette smoking and *on!* NP use), reasons to use or not use *on!* NPs, risk perceptions of use of a variety of tobacco products at the category level (eg, cigarettes, smokeless tobacco, and NPs), and respiratory symptoms. The main purpose of the 6-month follow-up survey is to collect information on participants’ posttrial tobacco use behaviors when they are no longer provided with *on!* NPs. None of our research questions rely on the 6-month follow-up survey.

Participants will be presented with the following debriefing statement at the conclusion of the study (ie, at the end of Week 6) or upon discontinuation of participation (ie, withdrawal from the study):

We would like to emphasize that in conducting this research, we were not trying to market, sell or promote a tobacco or nicotine product to you. Finally, oral tobacco-derived nicotine products should never be viewed as an alternative to quitting all tobacco products.

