### Limitations

One potential study limitation is that blinding is not feasible. Consequently, participants are aware of their group assignment. We use expired-air CO as our primary outcome to minimize potential biases in participants’ self-reported cigarette consumption. Another possible limitation is the relatively short study duration (ie, a total of 6 weeks). This study design aspect was a result of balancing feasibility and available resources while also providing sufficient time for participants to achieve a meaningful reduction in their cigarette consumption. Due to the relatively short study duration, we chose at least a 50% reduction in CO values as one of our primary outcomes—and abstinence as one of our secondary outcomes—considering we may not be able to observe the full course of smoking cessation. Previous studies using the same research products have shown measurable changes in smoking behavior in a similar timeframe [13]. Finally, this study uses a nonprobability sample, a common challenge of clinical trials. We try to mitigate these limitations by setting population quotas to align the sample with the adults who smoke cigarettes population in key demographic characteristics.

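### Baseline CO and cigarette use are recorded after open-label randomization, and nothing in the article says assignment is withheld until that window closes, so baseline may be affected by arm

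*Protocol article*

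**What the plan says.** Two sections of the protocol article give the same order of events.

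- **Baseline Assessment:** "After randomization and prior to week 1, participants will be asked to track their daily cigarette consumption via a web-based daily diary". The same paragraph asks for at least two CO readings over 3-7 days and adds: "These initial data will serve as baseline cigarette consumption and CO for subsequent comparisons".
- **Study Procedure:** at the telehealth session, "If eligible, they will be randomized to Group I or Group IIa/IIb". Next comes the window: "During the 3- to 7-day baseline assessment period, participants will provide CO readings every other day and record their cigarette consumption". Only then does product arrive: "Upon the completion of the baseline assessment period, participants will begin week 1 when they receive the research product".

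On blinding, the Overview states: "This study will use an open-label randomized controlled trial design". Limitations, after noting that blinding is not feasible, says: "Consequently, participants are aware of their group assignment".

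The only CO value described before randomization is the eligibility check at the telehealth session, "including a biometrically verified expired-air CO reading". The article does not use it as baseline.

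**The concern.** A baseline is protected by randomization only if assignment cannot influence it. Here it is measured after assignment, in participants who at some point know their arm. Someone who has just learned that they will get seven flavors, or only the unflavored product, might smoke more or less while waiting, report differently, or leave.

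The measurement carries a lot of weight in the plan:

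- It is the denominator of the ≥50% CO primary outcome (Outcome Measures).
- It is the denominator of the ≥50% cigarette outcome and of week-3 responder status (Outcome Measures; Figure 1 legend).
- It is the covariate in the linear regression for CO and in the estimating-equation model for cigarettes (Analytic Plan).
- It is the numeric CO value inserted after dropout (Analytic Plan).

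The Analytic Plan prefers baseline adjustment partly because it gives unbiased estimates. That property requires a covariate that assignment cannot affect. If assignment moves the covariate, adjustment carries the shift into the treatment estimate.

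The article relies on CO to offset the lack of blinding. An objective measure guards against misreporting, but not against a real change in smoking during the window.

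**Working it through.** **1. The plan's own figures (one-sided α 0.05, power 0.80).** With pooled variance under the null and no continuity correction,

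n = [1.645·√(2p̄(1−p̄)) + 0.842·√(p₁(1−p₁)+p₂(1−p₂))]² / (p₁−p₂)².

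- Week 3, 60% vs 45%: n = 135.996, so 136 per arm, as stated.
- Week 6, 80% vs 60%: n = 63.86, so 64 per arm, as stated.

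The sample size is not in dispute. The question is bias.

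**2. Illustration for the binary CO outcome at week 6, Group I (150) vs Group IIa (125).**

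From the Power section: 60% incidence in Group IIa, one-sided 5% test, and the group sizes. Assumed, and not in the documents: no flavor effect (so 60% in both arms), a Group IIa baseline 10% lower because of known assignment, and a lognormal week-6/baseline CO ratio with log-SD s of 0.6 to 1.0.

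Apparent incidence in Group IIa = Φ(z₀.₆₀ + ln(0.9)/s), with z₀.₆₀ = 0.2533 and ln(0.9) = −0.1054. The rejection rate is Φ[(p₁−p₂ − 1.645·SE₀)/SE₁], where SE₀ is pooled and SE₁ unpooled.

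| s | Shift in z | Apparent IIa incidence | Spurious difference | One-sided rejection |
|---|---|---|---|---|
| 0.6 | −0.176 | 53.1% | 6.9 points | 31% |
| 0.8 | −0.132 | 54.8% | 5.2 points | 22% |
| 1.0 | −0.105 | 55.9% | 4.1 points | 17% |

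For s = 0.6: SE₀ = 0.0600, SE₁ = 0.0599, and (0.0690 − 1.645 × 0.0600)/0.0599 = −0.495, which gives 0.31.

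**3. The same idea at week 3, Group I (150) vs combined Group II (250).** Take a 45% control rate, a Group I baseline 10% higher, no flavor effect and s from 0.5 to 1.0. Group I appears at 52.6% down to 48.8%. The spurious difference is 7.6 to 3.8 points, against a planned 15, and the rejection rate is 43% to 18%.

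**4. The opposite direction.** If the true week-3 rates are 60% vs 45%, power at 150 vs 250 is 89.9%. A Group I baseline 10% lower cuts it to 36.5% (s = 0.5) or 67.9% (s = 1.0).

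**5. Numeric CO.** The bias in the adjusted difference is slope × baseline shift. With an assumed baseline mean of 12-24 ppm, an assumed slope of 0.3-0.7 and a 10% shift, it runs from 0.3 × 1.2 = 0.36 ppm to 0.7 × 2.4 = 1.68 ppm. The Power section gives 1.7 ppm as the detectable difference, so this is 21% to 99% of it.

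**6. Which comparisons are exposed.** Objectives 1 and 4 compare Group I with all or part of Group II, whose product access differs from the start. The IIa vs IIb comparisons (objectives 2 and 3) are less exposed, because both groups receive only the unflavored product for weeks 1-3. CO-verified abstinence is defined by no smoking in the past 7 days and CO below 6 ppm, so it uses no baseline.

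**The case against.** The best defense is that one link is inferred. The bias needs participants to know their arm during the window. The statement in Limitations that they are aware of it explains the lack of blinding and does not say when they learn it. Product arrives only in week 1, so disclosure could coincide with delivery, and the risk would then largely disappear. That stands, and it limits confidence. It does not settle the matter, because the article describes no such withholding.

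The size is also hypothetical. No one has product during the window, and all arms await pouches of the same brand and strength, differing only in flavor access. The documents offer no evidence that this expectation moves CO by 10% in 3-7 days. That stands too: the calculation shows sensitivity, not likelihood.

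A reader might infer that every primary and secondary comparison is biased. The documents do not support that: abstinence needs no baseline, and IIa vs IIb is less exposed. A reader might also infer that the dropout rule fails altogether for anyone who leaves during the window. It does not: the binary rule counts dropouts as failures and needs no baseline value.

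**Conclusion.** The weakness in the order of steps is real and stated in two sections: what the plan calls baseline is measured after randomization in an open-label trial, with no stated withholding of assignment. If participants know their arm during the window, the Group I vs Group II comparisons on the baseline-dependent outcomes could be biased in either direction, and adjusting for that baseline would not remove the bias.

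Under the assumed 10% shift at week 6, the spurious difference is about 4-7 points and the one-sided rejection rate 17-31% instead of 5%. The shift, the log-SDs, the baseline means and the slopes are all assumptions; the actual size and sign are unknown. It would go too far to conclude that the trial's results are biased, because the article does not say when assignment is disclosed. Should-fix, medium confidence.

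**What to change.** **For participants not yet randomized:** randomize, or at least disclose the assignment, only after the 3-7 day window is complete. No extra visit is needed, because product is received only after the window.

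**For all participants:**

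- Tabulate baseline CO, baseline cigarette use and losses during the window by arm.
- Prespecify a sensitivity analysis of both primary CO outcomes with the pre-randomization telehealth CO reading as baseline.
- If assignment was in fact withheld until week 1, say so; that would answer most of the concern.

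**Costs and limits:** the telehealth value is a single reading, noisier than an average of two or more, and has no diary counterpart, so it cannot replace the baseline for cigarette outcomes or responder status. Reordering comes late: 314 of about 400 were enrolled by May 2024, so at most about 86 (86/400 = 21.5%) would be affected. It may add some shipping delay and would mix two baseline procedures in one trial. The tabulation and the sensitivity analysis use data already being collected.

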#### Weeks 1-6

In week 1, participants randomized into Group I will enter a 7-day period, during which they will receive 7 packs (20 pouches per pack) of research product (1 of each flavor) and instructed to try each flavor. This trial period is intended to allow participants to identify their preferred flavor(s) to use over the remainder of the study. After the trial period in week 1, Group I participants will complete 5 additional weeks of ad libitum product trial of research products (ie, weeks 2-6) with free choice of all flavors (up to 7 packs per week in any flavor combination of their choosing).

Likewise, following the baseline assessment, participants randomized into Group IIa and Group IIb will be provided with the Original variety of research products to use ad libitum for weeks 1-3 (up to 7 packs per week). At the end of week 3, participants in Group IIa will continue with the Original variety of research product for the remaining 3 weeks of the study (ie, weeks 4-6), and those in Group IIb will be provided access to all flavors of the research product. In week 4, Group IIb will have a 7-day trial period, during which they will receive 7 packs of research product (1 of each flavor) and instructed to try each flavor. As with Group I, this trial period is intended to allow Group IIb participants to identify their preferred flavor(s) to use over the remainder of the study. After the week-4 trial period, Group IIb will complete 2 weeks of ad libitum product trial of research products with free choice among all flavors (up to 7 packs of any combination per week).

Participants will be invited to complete a 6-month follow-up survey to gain insights about their tobacco use and related factors after the end of the product trial. This study will involve approximately 7 weeks (including the baseline period) of study participation in a home use test with daily surveys, weekly surveys, and a 6-month follow-up survey after the trial period.

